### Participants

The 80 patients with proteinuria will be recruited form National Scientific Medical Center, admitted to the internal medicine department. Age and gender matched 20 healthy volunteers will be enrolled from the outpatient clinics. The inclusion criteria are both male and female patients with any ethnic group, aged between 18 and 65 years old and newly diagnosed patients with glomerulonephritis and different range of proteinuria. The following exclusion criteria will be used: patients aged < 18 and > 65 years, glomerular filtration rate (GFR) < 60 ml/min, pregnant females, patients with diabetes mellitus, cancer, infectious diseases, and other life-treating comorbidities/conditions. Clinical and demographics data of the participants, medical history, comorbidities and data related to the disease will be recorded in case report forms.

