### SERS/Raman spectroscopy

Raman spectroscopy (Fig. 3) will perform using Horiba LabRAM HR Raman microscope with 785 nm laser excitation and × 100 or × 10 microscope objectives. The SERS spectroscopy will be performed on urine samples stirred with commercial 60 nm diameter gold nanoparticles (742,015, from Sigma Aldrich, UK). Prior to mixing with urine samples, those nanoparticles would go through three centrifugation/ resuspension cycles in order to remove stabilizing agents/reagents from the nanoparticle suspension as described in publication of Gudun et al., [24]. After stirring with urine, taken from patients, suspension of gold nanoparticles will be dropcasted on some spots on commercial gold film coated slides (CA134 from Dynasil Corp., USA), they will get dried and multiple Raman spectra will be measured on those spots for each sample with above mentioned Raman microscope and those spectra will be averaged.

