### Outcome measures

The primary outcome of the study is to develop and validate the Brillouin and SERS/Raman spectroscopy for non-contact urinary protein detection and protein profiling in patients with nephrotic syndrome. The secondary outcome of the study is identifying the most hazarded protein profiles associated with adverse outcomes.

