### Statistical analysis

All statistical analyses will be performed using STATA MP Version 15 (STATA Corporation, College Station, TX) statistical package. Two-sided *P-*values less than 0.05 will be reported as a significant for all analyses. Mean ± standard deviation (SD) for normal and median - interquartile range (IQR) for abnormal distribution of numerical variables will be shown in all data. Categorical variables will be presented as numbers (percentage). Categorical variables will be compared using Chi-square test or Fisher’s exact test and continuous variables will be compared using Kruskal–Wallis and/or Mann–Whitney U-test, as appropriate. Comparison of repeated two or more variables will be assessed with Wilcoxon and/or Friedman test as appropriate.

Obtained measurements of urinary protein by Brillouin and SERS/Raman spectroscopy will be compared with LC-MS data from same participant urine samples. Correlation between Brillouin and SERS/Raman spectroscopy parameters, LC-MS data and clinical-laboratory data of patients as well as healthy participants will be provided using Pearson’s or Spearman’s correlation as appropriate.

Univariate logistic regression will be used to test the association of several risk factors with high level of proteinuria. Multivariate logistic regression analysis will be used to assess the predictors for adverse outcomes. A receiver operator characteristics curve (ROC curve) analysis will be performed to identify the sensitivity, specificity, negative and positive predictive values of cut-off levels of Brillouin and SERS/Raman spectroscopy parameters in prediction of high proteinuria. Between measurement comparison of AUC will be provided with method developed by DeLong et al. [25].

During 1 year of follow-up, all adverse events such as exacerbation of proteinuria, progression of CKD, complications of nephrotic syndrome (thrombosis, nephrotic crisis, infection, including death), disease relapse rate and inefficacy of treatment regimen will be registered with referencing incident dates. Unadjusted and adjusted regression models will be evaluated to identify the association between urinary protein profiles defined by Brillouin and SERS/Raman spectroscopy and abovementioned adverse outcomes.

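### The comparison with LC-MS is specified only as a correlation that may pool patients with healthy volunteers, so it could show the group gap rather than how well the optical reading recovers protein in patients

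*Protocol article*

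**What the plan says.** The Outcome measures section sets the aim: "The primary outcome of the study is to develop and validate the Brillouin and SERS/Raman spectroscopy for non-contact urinary protein detection" and profiling, in patients with nephrotic syndrome. The Participants section gives the sample: "The 80 patients with proteinuria will be recruited", described as "newly diagnosed patients with glomerulonephritis and different range of proteinuria", and "Age and gender matched 20 healthy volunteers will be enrolled from the outpatient clinics".

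The Statistical analysis section says that the optical measurements will be compared with LC-MS on the same participants' urine, without naming a statistic in that sentence. The next sentence supplies one, Pearson's or Spearman's coefficient as appropriate: "Correlation between Brillouin and SERS/Raman spectroscopy parameters, LC-MS data and clinical-laboratory data of patients as well as healthy participants will be provided". The only threshold stated anywhere is that two-sided P-"values less than 0.05 will be reported as a significant for all analyses".

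Other evaluations are planned. They are ROC curves with DeLong comparison for high proteinuria, separate measurement of molecular-weight fractions by the hybrid system, and a measurement-validation stage of 10-14 months before recruitment.

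**The concern.** Two features of the LC-MS comparison are badly fixed.

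First, the population. The reference quantity, urinary protein, separates the two groups by design. If the optical reading also separates them, for whatever reason, a coefficient over all 100 people picks up the distance between the two clusters. It can then be clearly non-zero when the optical reading carries no information about protein among patients, and patients are the group the primary outcome names. The wording allows this analysis and does not exclude it.

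Second, the statistic. A correlation coefficient, with or without its p-value, does not say how far an optical reading would miss the true protein level. A sensor meant to monitor patients' urine needs that error.

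At stake is whether the reported agreement with LC-MS reflects what the instrument measures or who was recruited.

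**Working it through.** The article states no expected correlation, agreement limit or sample-size basis, so there is no planned figure to reproduce. The check is on the mechanism.

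**Inputs**
- From Participants: 80 patients and 20 healthy volunteers, so the patient share is p = 0.8 and p(1 - p) = 0.16.
- From Statistical analysis: two-sided 0.05.
- Assumption, because the article gives no distributions: patients and volunteers differ by d within-group SDs on each method, d is varied, and the true correlation inside each group is zero.

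**Step 1: smallest significant correlation.** Critical |r| = t / sqrt(t² + n - 2), with t the 97.5% point on n - 2 degrees of freedom.
- n = 100: 0.197, or 0.197² = 3.9% shared variance.
- n = 80: 0.220, or 0.220² = 4.8% shared variance.

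**Step 2: pooled correlation produced by the gap alone.** With equal gaps, r = 0.16d² / (1 + 0.16d²).
- d = 1: 0.16 / 1.16 = 0.14
- d = 2: 0.64 / 1.64 = 0.39
- d = 3: 1.44 / 2.44 = 0.59

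The expected r passes 0.197 when d = sqrt[0.197 / (0.803 × 0.16)], about 1.24 SD.

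**Step 3: how often it is significant.** Simulation with 80 + 20 normal observations, equal SDs and 4,000 runs per row:

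| Gap on the two methods (SD) | Pooled Pearson r | Pearson significant | Mean Spearman | Spearman significant |
|---|---|---|---|---|
| 0 and 2 | 0.00 | 4% | 0.00 | 5% |
| 0.5 and 0.5 | 0.04 | 7% | 0.04 | 7% |
| 1 and 1 | 0.14 | 28% | 0.13 | 25% |
| 1 and 2 | 0.23 | 66% | 0.21 | 56% |
| 2 and 2 | 0.39 | 99% | 0.34 | 96% |
| 3 and 3 | 0.59 | 100% | 0.45 | 100% |

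Spearman levels off at about 0.48 even under complete separation. Demanding a high rank correlation would therefore limit the problem, but the article sets no such level.

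**Step 4: the same data, patients only.** Restricted to the 80 patients, the rate was 4.4% to 5.7% at every gap tried. By the Fisher z approximation, power for a true within-patient correlation of 0.30 is Φ(atanh(0.30) × sqrt(77) - 1.96) = Φ(0.76), about 78%. For 0.31 it is about 80%. The planned number of patients can support a patients-only analysis.

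**The case against.** The strongest reply is that pooling is nowhere stated. The sentence can equally mean that each group gets its own coefficient, and then Steps 2 and 3 do not apply. That is correct, and the point is only that the text permits pooling. The reply does not touch the choice of statistic: by group or not, a correlation does not measure error.

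A second reply is that the false-positive scenario is extreme. Volunteers are age and gender matched, patients with low GFR, diabetes, cancer or infection are excluded, and patients are recruited over a range of proteinuria. An optical reading about 2 SD apart between groups yet unrelated to protein within patients may be unlikely. This also stands, and it is why the result is given over a range of gaps, including one where nothing goes wrong.

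A third reply is that an article leaves detail to a fuller protocol or analysis plan. That is fair for the form of a calibration model. It is less so for the population and statistic of the main comparison, which the article does describe.

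Several stronger conclusions might be inferred, and the article does not support them:
- **Correlation is the only validation method.** It is not, given the ROC analyses, the fraction measurements and the technical stage. It is the only statistic tied explicitly to LC-MS. The ROC target is high proteinuria, and neither the fraction work nor the technical stage states a within-patient measure of error against LC-MS.
- **P < 0.05 is the test of being validated.** The article says only that such values are reported as significant.
- **Urine dilution would drive a positive result.** The remark on urea, creatinine and uric acid concerns conventional Raman, and comparing a dilution-dependent reading with creatinine-indexed ratios would ordinarily add noise.
- **Averaging the SERS spectra loses the repeatability data.** The article says that "multiple Raman spectra will be measured on those spots for each sample" and are then averaged. It does not say that the individual spectra are discarded, and the validation stage may cover repeatability.

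**Conclusion.** The concern holds in a limited form. The article ties only a correlation to the LC-MS comparison, leaves open whether it pools 80 patients with 20 healthy volunteers, and names no measure of calibration or prediction error against LC-MS, although the primary outcome is about patients.

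The size of the problem depends on two conditions: that the groups are pooled, and that both methods separate them. The false-positive rate is about a quarter at a 1 SD gap on both methods, nearly certain at 2 SD or more, and nominal if the optical method does not separate the groups. The gaps, the normal distributions and the zero within-group correlation are assumptions, not figures from the article.

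It would go too far to conclude that a method tracking nothing in patients will be declared validated. The text shows only that the stated comparison could not rule this out. This is a cheap and worthwhile improvement rather than a flaw that invalidates the study.

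**What to change.** In the Statistical analysis section:

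1. State that the primary comparison of Brillouin and SERS parameters with LC-MS abundance, or with measured urinary protein, is made within the 80 patients.
2. Report the healthy volunteers separately, as an analysis of how well the optical parameters discriminate patients from volunteers.
3. Regress log protein on the optical parameters and report cross-validated prediction error. Any selection of spectral bands belongs inside the cross-validation. Limits of agreement make sense only after the optical readings have been converted to protein units, because frequency shift, band intensity and protein abundance are not on one scale.
4. Keep Pearson and Spearman coefficients as descriptive, by group, with confidence intervals.

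This uses samples and assays already planned. The cost is revised wording, a little more analysis work, and headline correlations that will probably be smaller than pooled ones.

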### Blood and urine samples

Full blood biochemistry and corresponding urinalysis will provide additional information about participant health condition, such as functional condition of liver, kidney, heart, metabolic status etc. These widely evaluated routine laboratory data will be obtained from all participants. Routine blood metabolic profile including total protein, albumin, renal and liver function tests, coagulation tests, lipid profiles as well as urinalysis, proteinuria, albumin to creatinine ratio (ACR) and protein to creatinine ratio (PCR) will be performed at the study enrollment. Control renal function tests and ACR or PCR will be performed at the end of the follow up period. All blood and urine samples from participants will be collected at the time of hospital admission or at the visits to outpatient clinic. All blood and urine samples will be stored at -80co freezers for proper preservation before further visco-elastic and chemical analysis will be performed. After last patient is enrolled to the study, all laboratory evaluations will be provided according to the study protocol.

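### The supporting risk-factor analysis reduces continuously measured proteinuria to 'high' or not and tests one factor at a time, losing about 36–51% of the information in that regression under stated assumptions

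*Protocol article*

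**What the plan says.** All references are to the protocol article.

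- **Risk-factor analysis** (Statistical analysis): "Univariate logistic regression will be used to test the association of several risk factors with high level of proteinuria". The outcome is therefore binary, and factors enter singly.
- **Measurement** (Blood and urine samples): "proteinuria, albumin to creatinine ratio (ACR) and protein to creatinine ratio (PCR) will be performed at the study enrollment". These are quantities.
- **Sample** (Participants): "The 80 patients with proteinuria will be recruited", described as "newly diagnosed patients with glomerulonephritis and different range of proteinuria". In addition, "Age and gender matched 20 healthy volunteers will be enrolled from the outpatient clinics".
- **Second use of the binary outcome** (Statistical analysis): the ROC analysis evaluates "cut-off levels of Brillouin and SERS/Raman spectroscopy parameters in prediction of high proteinuria".
- **Test level** (Statistical analysis): "Two-sided *P-*values less than 0.05 will be reported as a significant for all analyses".
- **Adjusted models** (Statistical analysis): multivariate logistic regression and the adjusted regression models are both assigned to adverse outcomes. Neither is assigned to proteinuria level.
- **Continuous analysis** (Statistical analysis): Pearson or Spearman correlations are planned among spectroscopy parameters, LC-MS data and clinical-laboratory data, covering patients and healthy participants.

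**The concern.** The study recruits deliberately across the range of proteinuria and measures it on a continuous scale. The risk-factor regression then treats all patients above a cut as alike, and all below it as alike. Two things follow.

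First, precision and power fall, and the result depends on where the cut lies. The loss arises wherever the cut is placed, so the point does not rest on the absence of a threshold from a condensed article.

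Second, with one factor at a time, each factor absorbs the effect of any factor correlated with it. No planned analysis would show which factors relate independently to proteinuria level. With 80 patients there is little precision to give away.

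**Working it through.** The article gives no power or effect size for this analysis, so there is no stated figure to reproduce. The loss can be calculated under explicit assumptions.

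**Inputs from the article:** 80 patients; two-sided 0.05; binary outcome; one predictor per model.

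**Assumptions not in the article:** log PCR approximately normal; a continuous, linearly related predictor; a share p of patients classed as high, ranged over 20–50%.

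**Step 1. Efficiency of the dichotomised analysis.** Relative to the continuous analysis, efficiency = φ(z_p)² / [p(1 − p)], where φ is the standard normal density at the cut.

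- p = 0.50: 0.3989² / 0.25 = 0.637
- p = 0.20: 0.2800² / 0.16 = 0.490

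| Share high | Efficiency | Information lost | 80 patients act like | Dichotomised n to match 80 |
|---|---|---|---|---|
| 50% | 0.637 | 36.3% | 50.9 | 126 |
| 40% | 0.622 | 37.8% | 49.8 | 129 |
| 30% | 0.576 | 42.4% | 46.1 | 139 |
| 25% | 0.539 | 46.1% | 43.1 | 149 |
| 20% | 0.490 | 51.0% | 39.2 | 164 |
| 10% | 0.342 | 65.8% | 27.4 | 234 |

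The formula is symmetric in p and 1 − p, so classing 80% as high costs as much as classing 20%. The 10% row lies outside the assumed range and shows that more extreme cuts cost more.

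**Step 2. Power by simulation.** n = 80, 3000 runs per scenario; Pearson test on continuous proteinuria against the likelihood-ratio test from a univariate logistic regression.

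| True correlation | Continuous | 50% high | 30% high | 20% high |
|---|---|---|---|---|
| 0.20 | 44% | 31% | 28% | 24% |
| 0.30 | 77% | 60% | 55% | 47% |
| 0.40 | 96% | 85% | 81% | 73% |

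At a correlation of 0.30 the loss is 77 − 60 = 17 points for a median split and 77 − 47 = 30 points with 20% high.

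**Step 3. What 80 patients can detect.** By Fisher's z, the correlation detectable with 80% power is tanh[(1.960 + 0.842)/√77] = 0.31. Simulated power there is 81% continuous, against 61%, 56% and 50% with 50%, 30% and 20% classed as high.

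**Step 4. Does another planned analysis fill the gap?** The correlations keep proteinuria continuous but compare two variables at a time without adjustment. As worded they also take in the healthy participants, so part of a correlation could reflect the patient–healthy difference. The adjusted models are for adverse outcomes. None is an adjusted model of proteinuria level in the 80 patients.

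**The case against.** The strongest reply is that the same section already plans continuous correlations between spectroscopy and clinical-laboratory data, which would include ACR and PCR. A reader might infer from the figures above that the whole study loses a third to a half of its information. The article does not support that: the continuous column in Step 2 is close to a test the plan already contains for spectroscopy parameters. This part of the reply stands. What it leaves is the risk-factor regression and the missing adjusted model.

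Next, this is a supporting analysis. Under Outcome measures, the primary outcome is development and validation of the spectroscopy, and the secondary outcome concerns protein profiles and adverse outcomes. Risk factors for high proteinuria are neither. That also stands and limits the importance of the point.

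A reader might also infer that including the healthy volunteers would turn the regression into a patient-versus-healthy contrast. The article does not say they enter this model. Even if they did, a median split of the patients gives a low group of 40 patients plus 20 volunteers, so two-thirds are patients; with 20% high it is 64 plus 20. The inference would need nearly all patients to be classed as high.

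Nor is the binary outcome without use. It is the target for sensitivity, specificity and predictive values, and odds ratios for the same target are easy to set beside the ROC results. That is a reason to keep it for the ROC analysis, not to make it the only regression outcome for proteinuria level.

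Finally, a condensed article may leave the threshold and factor list to a fuller document. That is accepted, and neither is criticised here. The binary outcome and the univariate method are stated choices.

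**Conclusion.** The point holds, limited to the supporting risk-factor regression. The article fixes a binary outcome and single-factor models for a quantity that it measures continuously and samples across its range, and it plans no adjusted model of proteinuria level. The loss in this regression is about 36–51% of the information, so 80 patients act like about 51 to 39. At a true correlation of 0.30, power falls from about 77% to between 60% and 47%.

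These sizes rest on approximately normal log PCR, a linear association with a continuous predictor, and 20–50% of patients classed as high. None of these is given in the article. The direction of the loss does not depend on the exact cut; its size does. The primary and secondary outcomes are not affected by this finding, and the planned correlations are not subject to the loss.

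**What to change.** In the 80 patients, replace the univariate logistic regression with linear regression of log PCR (or log ACR) on a small prespecified set of clinical risk factors, reported unadjusted and adjusted. It stays a supporting analysis.

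Relate BLS and SERS parameters to log PCR in separate models. The article's Discussion presents Brillouin spectroscopy as a possible way to quantify total protein, so such a parameter may be a readout of the outcome itself. Adjusting a risk factor for it could remove the association under test, and adding many spectral parameters could overload a model of 80 patients.

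Keep a prespecified high-proteinuria threshold for the ROC analysis.

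The cost is a short change of analysis wording and a decision on the factor list; no new data are needed. The downside is that effects are reported as ratios of PCR rather than as odds ratios for the ROC target.

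### Standard multivariable logistic regression for adverse outcomes in at most 80 patients probably overstates true associations; Firth estimation with profile-likelihood inference largely corrects this

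*Protocol article*

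**What the plan says.** Under Participants, "The 80 patients with proteinuria will be recruited". The same section adds: "Age and gender matched 20 healthy volunteers will be enrolled from the outpatient clinics". The controls are not expected to have relapse, progression or treatment failure, so 80 is the ceiling for the outcome models.

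Under Outcome measures: "The secondary outcome of the study is identifying the most hazarded protein profiles associated with adverse outcomes".

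The Statistical analysis section names the method: "Multivariate logistic regression analysis will be used to assess the predictors for adverse outcomes". It goes on: "Unadjusted and adjusted regression models will be evaluated to identify the association between urinary protein profiles", as defined by the two spectroscopies, and the adverse outcomes. That second sentence does not give the type of regression. Two-sided P-values "less than 0.05 will be reported as a significant for all analyses". The outcomes are collected over one year and cover exacerbation of proteinuria, CKD progression, nephrotic complications including death, relapse and treatment inefficacy.

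The article gives no expected outcome rate, no number of model terms and no estimator other than logistic regression.

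**The concern.** Maximum-likelihood estimates in logistic regression have a small-sample bias away from zero. It grows as the number of events per estimated term falls. Several features of the design point to few events per term:

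- At most 80 patients contribute outcomes. They are newly diagnosed, a GFR below 60 ml/min is an exclusion, and follow-up is one year.
- Several distinct outcomes are listed. Modelled separately, each has no more events than a composite would.
- Candidate predictors come from Brillouin, SERS/Raman and LC-MS measurements, with adjustment terms on top.

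The odds ratios decide which protein profiles are reported as most hazardous. The article also hopes to carry the findings towards a prognostic tool. Systematically overstated odds ratios would exaggerate how strongly the truly associated profiles relate to outcome.

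**Working it through.** The article reports no figure on this point, so there is nothing to reproduce.

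**Inputs from the article:** 80 patients as an upper limit; two-sided 0.05; one-year follow-up; multivariable logistic regression.

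**Assumptions, because the article is silent:** outcome rate 10–50%; 2–8 model terms; true odds ratio 2.0 per SD (log 0.693) or, in a second set of runs, true log odds ratio 0.6; no dropout.

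**Step 1. Events per term.** Events = 80 × rate.

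| Rate | Events | Events per term, 5 terms |
|---|---|---|
| 10% | 8 | 1.6 |
| 20% | 16 | 3.2 |
| 30% | 24 | 4.8 |
| 40% | 32 | 6.4 |
| 50% | 40 | 8.0 |

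**Step 2. Size of the bias, true odds ratio 2.0.** Simulation with 2,000 data sets per scenario, n = 80 and normal predictors with correlation 0.3. The other predictors alternate between odds ratios of 1.5 and 1.0. Odds ratios are geometric means, and bias = (mean estimated log OR − 0.693) / 0.693.

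| Events / terms | Events per term | ML odds ratio | ML bias (log scale) | Firth odds ratio |
|---|---|---|---|---|
| 40 / 2 | 20 | 2.08 | +5% | 1.98 |
| 20 / 2 | 10 | 2.12 | +8% | 2.01 |
| 40 / 4 | 10 | 2.17 | +12% | 2.02 |
| 40 / 8 | 5 | 2.31 | +21% | 2.01 |
| 20 / 5 | 4 | 2.25 | +17% | 2.03 |
| 8 / 3 | 2.7 | 2.29 | +19% | 2.02 |
| 20 / 8 | 2.5 | 2.38 | +25% | 1.98 |
| 12 / 5 | 2.4 | 2.35 | +23% | 2.03 |

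Worked example, 20 events and 5 terms: ln 2.25 = 0.811, and (0.811 − 0.693) / 0.693 = 0.17.

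**Step 3. Second set of runs, true log odds ratio 0.6**, over 8–40 events and 2–8 terms. The ML bias was about 5–12% with 2 terms and about 14–34% with 5–8 terms. Firth was within roughly −8% to +5% and had the lower root mean squared error (RMSE) in every setting. On the odds-ratio scale, a true exp(0.6) = 1.82 becomes exp(0.6 × 1.05) = 1.88 to exp(0.6 × 1.12) = 1.96 with 2 terms, and exp(0.6 × 1.14) = 1.98 to exp(0.6 × 1.34) = 2.23 with 5–8 terms. The lower ends are not hard bounds: a further setup, with three predictors at 0.6 and the rest null, gave 10% at 24 events and 5 terms.

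**Step 4. Null predictors.** With a true odds ratio of 1 and 5 terms (12 or 20 events), the ML geometric mean was 1.01–1.02 and the rejection rate 4.3–4.9%.

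**Step 5. What Firth costs.**

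- With Wald tests it rejected about 3 to 10 points less often than ML for a true odds ratio of 2.0 (55.9% to 49.5% at 20 events and 5 terms; 58.8% to 48.6% at 40 events and 8 terms).
- With penalised profile-likelihood tests, rejection stayed within about 3 points of the ML Wald test, and null rejection was 4–6%.
- For outcome rates of 10–25%, mean predicted risk was 0.7–1.8 points above the observed rate. At 50% the shift was about zero.
- RMSE fell, for example from 0.46 to 0.37 at 20 events and 5 terms.

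**The case against.** Multivariable logistic regression is conventional for a secondary, association-type aim. The article does not say maximum likelihood, and a predictor list or model-size limit may sit in an analysis plan that is not shown. Absence of such a list is therefore not held against the article. The method itself is named, however, and without a qualifier it means the ordinary fit.

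A second objection is size. With 2–3 terms and 16–40 events, the inflation is only 4–11% of the log odds ratio, about a fifth of a standard error or less. Even at 20 events and 5 terms the bias of 0.811 − 0.693 = 0.118 is about a quarter of the RMSE (0.118 / 0.46 = 0.26), and ML interval coverage stayed at 94.6–96.6%. This stands: the bias is an average, it is modest for small models, and it does not invalidate the intervals. A composite outcome could also bring more events than any single one.

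Two stronger readings are tempting, and neither is supported:

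- A reader might infer that inflated odds ratios make null profiles look prognostic. Step 4 shows that they do not.
- A reader might add that the apparent AUC of the outcome model will be optimistic. The article plans ROC analysis for high proteinuria and states none for the adverse-outcome model, so this matters only if discrimination of that model is reported.

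The power objection to Firth rests on Wald tests and mostly disappears with profile-likelihood tests.

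**Conclusion.** The point holds in limited form. With at most 80 patients, the model as named is likely to overstate non-null associations: on average by about 5–12% of the log odds ratio with 2 terms and about 14–34% with 5–8 terms, over an assumed 8–40 events. Null odds ratios are not affected. The direction is secure, but the size rests on event counts, model sizes, effect sizes and predictor correlations that the article does not give. It would be too strong to say that inflated odds ratios are certain, or that the bias is material for every plausible model.

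Firth estimation corrects bias but adds no information. For a single predictor under the null approximation, SE = 1/√(80 × rate × (1 − rate)) is 0.37, 0.26 and 0.22 at 8, 20 and 40 events. The odds ratio per SD detectable with 80% power, exp[(1.96 + 0.84) × SE], is then about 2.8, 2.1 and 1.9. Keeping the model small therefore matters as much as the choice of estimator.

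**What to change.** In the Statistical analysis section, state that the logistic models for adverse outcomes use Firth penalised-likelihood estimation, with penalised profile-likelihood confidence intervals and tests instead of Wald ones. State also that they use a small predictor set, sized to the expected number of events and fixed before laboratory and outcome data are linked. The blinding of the laboratory team to clinical data, promised in the Ethics statement, makes that timing practical.

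Ridge regression is not an equivalent choice here. In the true-odds-ratio-2.0 runs (400 data sets each, cross-validated penalty) it biased log odds ratios by −19% to −38%, and its ordinary 95% intervals covered only 66–81% of the time.

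The change needs no further patients or assays. It has a price: reported odds ratios become slightly smaller, power changes by at most a few points, and the intercept must be corrected if absolute risks are predicted. If discrimination of these models is ever reported, it should be corrected for optimism.
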